# The Effects of Positive Affect and Episodic Future Thinking on Temporal Discounting and Healthy Food Demand and Choice Among Overweight and Obese Individuals: Protocol for a Pilot 2×2 Factorial Randomized Controlled Study

**DOI:** 10.2196/12265

**Published:** 2019-03-20

**Keywords:** obesity, cancer, temporal discounting, food choice, eating behavior, episodic future thinking, positive affect, guided imagery, randomized controlled trial

## Abstract

**Background:**

Unhealthy behaviors (eg, poor food choices) contribute to obesity and numerous negative health outcomes, including multiple types of cancer and cardiovascular and metabolic diseases. To promote healthy food choice, diet interventions should build on the dual-system model to target the regulation and reward mechanisms that guide eating behavior. Episodic future thinking (EFT) has been shown to strengthen regulation mechanisms by reducing unhealthy food choice and temporal discounting (TD), a process of placing greater value on smaller immediate rewards over larger future rewards. However, these interventions do not target the reward mechanisms that could support healthy eating and strengthen the impact of EFT-anchored programs. Increasing positive affect (PosA) related to healthy food choices may target reward mechanisms by enhancing the rewarding effects of healthy eating. An intervention that increases self-regulation regarding unhealthy foods and the reward value of healthy foods will likely have a greater impact on eating behavior compared with interventions focused on either process alone.

**Objective:**

This study aimed to introduce a protocol that tests the independent and interactive effects of EFT and PosA on TD, food choice, and food demand in overweight and obese adults.

**Methods:**

This protocol describes a factorial, randomized, controlled pilot study that employs a 2 (affective imagery: positive, neutral) by 2 (EFT: yes, no) design in which participants are randomized to 1 of 4 guided imagery intervention arms. In total, 156 eligible participants will complete 2 lab visits separated by 5 days. At visit 1, participants complete surveys; listen to the audio guided imagery intervention; and complete TD, food demand, and food choice tasks. At visit 2, participants complete TD, food demand, and food choice tasks and surveys. Participants complete a daily food frequency questionnaire between visits 1 and 2. Analyses will compare primary outcome measures at baseline, postintervention, and at follow-up across treatment arms.

**Results:**

Funding notification was received on April 27, 2017, and the protocol was approved by the institutional review board on October 6, 2017. Feasibility testing of the protocol was conducted from February 21, 2018, to April 18, 2018, among the first 32 participants. As no major protocol changes were required at the end of the feasibility phase, these 32 participants were included in the target sample of 156 participants. Recruitment, therefore, continued immediately after the feasibility phase. When this manuscript was submitted, 84 participants had completed the protocol.

**Conclusions:**

Our research goal is to develop novel, theory-based interventions to promote and improve healthy decision-making and behaviors. The findings will advance decision-making research and have the potential to generate new neuroscience and psychological research to further understand these mechanisms and their interactions.

**Trial Registration:**

ISRCTN Registry ISRCTN11704675; http://www.isrctn.com/ISRCTN11704675 (Archived by WebCite at http://www.webcitation.org/760ouOoKG)

**International Registered Report Identifier (IRRID):**

DERR1-10.2196/12265

## Introduction

### Background and Rationale

Unhealthy behaviors, such as poor food choices and physical inactivity, are associated with numerous negative health outcomes, including, but not limited to, multiple types of cancer and cardiovascular and metabolic diseases [1]. Notably, these behaviors can contribute to weight gain and obesity, which remains one of the top preventable causes of morbidity and mortality worldwide [2,3]. Only 9-13% of US adults met fruit and vegetable intake recommendations (ie, 1.5 to 2 cups of fruits a day, 2 to 3 cups of vegetables a day) in 2013 [4]. Similarly, in England, only 26% of adults consumed 5 or more portions of fruits and vegetables a day in 2016 [5]. Interventions targeting diet may help individuals lose weight in the short term, but often have minimal impact on weight loss maintenance, potentially because they do not target the underlying cognitive and affective mechanisms of eating behavior [6].

Eating behavior is a complex process regulated by homeostatic, physiologic-driven mechanisms that drive eating in response to hunger [7] and nonhomeostatic, reward-driven mechanisms that drive eating in response to highly palatable external cues (eg, foods high in fat and sugar) [8]. The rewarding nature of highly palatable foods can lead to eating in the absence of hunger, and in turn, overeating can result in increased reward responsivity to certain foods and subsequent weight gain [9]. Dual-system neural models of eating behavior theorize that the increased neural reward responsivity can be mitigated by activating areas of the brain associated with regulation to dampen hyperactive reward responses and manage unhealthy eating behaviors [10]. The regulation network, referred to as the *executive* [11], *deliberative* [12], or *reflective* system [13], includes brain regions associated with cognitive control, emotion regulation, and goal-directed behavior. In contrast, the reward network, referred to as the *impulsive* [11,13] or *automatic* [12] system, includes brain regions associated with evaluating, anticipating, and processing rewards. When there is an imbalance between these networks, the reward network can override the regulation network, whereby overeating leads to weight gain and eventually obesity [14]. Thus, among obese individuals, the regulation network is often considered underactive and the reward network is considered overactive [14].

To promote the healthy diet of fruits, vegetables, legumes, nuts and whole grains, and minimal sugars and fats recommended by the World Health Organization [15], healthy eating interventions should build on the dual-system model described above to target both the regulation and reward mechanisms that guide eating behavior. One regulation mechanism relevant to food choice is delayed gratification—the ability to resist the temptation of an immediate reward (eg, highly palatable food) in preference of a later reward (eg, long-term health) [10]. Prior research suggests that individuals who are obese show poor delayed gratification and demonstrate greater temporal discounting (TD), meaning they place greater value on smaller immediate rewards over larger or delayed rewards in the future [16-18]. For example, an individual with a low delay of gratification may value the satisfying taste of savory or sweet food that is available now, over the health benefits of future weight loss. Prior work indicates increased brain activation in regulation regions when participants make decisions involving delayed rewards and increased activation in reward regions when participants make decisions involving immediately available rewards [19]. Decreasing TD may, therefore, make it easier to favor the long-term reward of making a healthy food choice over the immediately available taste reward that may be associated with unhealthy food choice.

Multiple studies have demonstrated that the cognitive process of episodic future thinking (EFT; ie, the ability to imagine or simulate personal experiences that might occur in one’s future) reduces TD, especially in overweight and obese individuals [20]. Research delving into the mechanisms of EFT suggests that EFT is derived from episodic memory, which supports future simulation by allowing people to flexibly retrieve and recombine elements of past experiences into novel representations of events that might occur in the future [21]. Evidence from thought sampling procedures indicates that episodic future thoughts occur frequently in everyday life and serve a range of functions, including decision making, emotion regulation, intention formation, and planning [21]. Furthermore, training in EFT (vs episodic recent thinking [ERT]) has been shown to reduce discounting rates and food reinforcement [22] as well as behavioral outcomes such as calorie consumption [23,24]. These lab studies and pilot interventions suggest that EFT has the capacity to reduce TD and calorie consumption; yet, these interventions do not target the reward mechanisms that impact eating decisions. In addition, targeting the reward mechanisms involved in food choice could strengthen the impact of an EFT-anchored intervention.

One way to target the reward mechanisms involved in obesity is by enhancing the rewarding effects of healthy eating and creating positive associations with healthy food. Descriptive and observational research has shown that positive affect (PosA) is associated with healthier food [25,26], but this association may be bidirectional, with some studies showing fruit and vegetable consumption predicting PosA [27,28]. Affect is the representation of the body’s core evaluation, at any level and in any modality (including physiological reactions, emotions, thoughts, and expressions), that an object, event, or person encountered in the world is good for it, bad for it, approachable, or avoidable [29]. Accordingly, PosA is the physiological and emotional experience that an object is beneficial and confers positive value to the body and self. Importantly, a study experimentally manipulating PosA showed that creating positive associations with fruit (as opposed to neutral or negative associations) significantly increased the likelihood of choosing fruit in a behavioral choice task [30]. Consistent with the dual-system model, eating behavior interventions may need to take advantage of the overactive reward system that has been associated with overeating and obesity by enhancing the rewarding associations with healthy eating and its effects.

PosA has also been shown to increase TD [31], indicating that EFT exercises and feelings of PosA may have an interactive or additive effect on discounting rates. Both mechanisms have different underlying neurological pathways, and their interactive effect has not been tested to date. Although programs and interventions to increase healthy food choices exist, new interventions firmly grounded in behavioral, cognitive, affective, and neuroscientific theory may have a stronger impact on increasing healthy food choices than existing interventions. An intervention focused on enhancing both reward for healthy foods and regulation for unhealthy foods is likely to have a greater impact on dietary choices compared with interventions focused on either process alone.

### This Study

This protocol aims to test whether an intervention focused on enhancing both the reward value of healthy foods and regulation surrounding unhealthy foods is likely to have a stronger effect on eating behavior compared with interventions focused on either process alone. To achieve this, we will conduct a 2×2 factorial, randomized, controlled lab-based intervention study of brief guided imagery exercises that target regulation (EFT: yes, no) and reward (PosA imagery: positive, neutral) mechanisms of eating behavior.

To assess the individual and combined effects of EFT and PosA on eating behavior, we will examine the effect of PosA, EFT, and their interaction on (1) TD, (2) the reward value of healthy and unhealthy foods (ie, food demand indexed by intensity or the number of items consumed when freely available), and (3) food choice. Our predictions are 3-fold. First, we predict that participants in the EFT condition will demonstrate lower TD, lower demand for unhealthy foods, higher demand for healthy foods, more healthy food choices, and less unhealthy food choices compared with the ERT condition. Second, we predict that participants in the PosA condition will demonstrate no differences in TD, yet exhibit lower demand for unhealthy foods, higher demand for healthy foods, more healthy food choices, and less unhealthy food choices compared with the neutral affect conditions. Third, we predict that participants in the EFT and PosA conditions will demonstrate the lowest TD, the lowest demand for unhealthy foods, the highest demand for healthy foods, the healthiest food choices, and the least unhealthy food choices compared with participants in all other conditions.

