### Analysis

#### Primary Statistical Analysis

Our primary statistical analyses will comprise a mixed design (between-subjects and repeated measure) that compares TD, food demand, and food choice measures at baseline, after allocation, and at closeout across treatment arms. Our analyses will control for standard demographic variables such as age, biological sex, race, and income. A series of repeated measure ANOVAs with treatment arm as a between-subject variable and measurement period as the repeated measure will be conducted on TD rates and healthy and unhealthy food demand indices, respectively.

In addition, to examine the effect of the intervention arms on food choices inside and outside the lab, a series of ANOVAs will be conducted on healthy and unhealthy snack food choices and average daily serving intake values for each of the food categories. To probe the effect of the intervention on in-lab food choices, we will conduct a repeated measure ANOVA with measurement period repeated across treatment group on health and unhealthy snack food choices. Next, to probe the effect of the intervention on food choices outside the lab, we will conduct a 1-way ANOVA with treatment arm entered as the between-subject variable on average daily serving intake values for the primary food categories (ie, fruit and vegetable intake).

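### The prediction that PosA makes no difference to TD cannot be supported by the planned difference tests, and the text does not say which PosA comparison it concerns

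*Protocol article*

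**What the plan says.** The section This Study (Introduction) makes three predictions about TD.

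- Prediction 1: "First, we predict that participants in the EFT condition will demonstrate lower TD" than the recent-thinking (ERT) condition.
- Prediction 2: "Second, we predict that participants in the PosA condition will demonstrate no differences in TD, yet exhibit lower demand for unhealthy foods". The words at issue are "will demonstrate no differences in TD". Its list of outcomes ends with the comparator: "less unhealthy food choices compared with the neutral affect conditions".
- Prediction 3: "Third, we predict that participants in the EFT and PosA conditions will demonstrate the lowest TD", relative to every other condition.

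The same section aims to examine PosA, EFT and their interaction. Background and Rationale cites a study in which "PosA has also been shown to increase TD" and infers an interactive or additive effect. Findings and Implications (Discussion) expects synergy.

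For TD, Primary Statistical Analysis plans "A series of repeated measure ANOVAs with treatment arm as a between-subject variable" and measurement period as the repeated factor. Sample Size gives 124 analysed (31 per arm) and 95% power to detect an arm-by-period interaction with a standardized effect size of 0.17.

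**The concern.** Prediction 2 is a null prediction on a primary outcome. The analysis and the sample size are both built to detect differences, so the prediction can only appear to hold through a failure to reject. That outcome is likely whenever the true PosA effect is small to moderate, whether or not it is zero.

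The article also does not settle which contrast prediction 2 describes. It could be the PosA factor pooled over EFT (arms 1 and 2 against arms 3 and 4) or PosA alone against the control (arm 2 against arm 4). The readings have different implications for prediction 3 and different precision. At stake is whether the trial can say that PosA leaves TD alone, which is part of its account of two separate mechanisms.

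**Working it through.** **Inputs.** From Sample Size: 124 analysed, 31 per arm, hence 62 versus 62 for the PosA main effect; effect size 0.17; alpha 0.05; 4 arms; 3 periods. Assumed, because the article gives no value: TD scaled to SD 1, correlation 0.5 between periods, sphericity, and all equivalence margins.

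**1. The stated power.** Read 0.17 as Cohen's f for the arm-by-period interaction. Noncentrality = f² × N × m/(1 − rho) = 0.0289 × 124 × 3/0.5 = 21.5, with 6 and 240 degrees of freedom. Power is 0.951, which reproduces the stated 95%. With rho = 0.3 it would be 0.84, and with rho = 0 it would be 0.67. Attrition also reproduces: 31/0.8 rounds up to 39 per arm, or 156.

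**2. The planned size as a PosA effect.** Suppose only PosA acts, shifting TD by d at both periods after a common baseline. The interaction variance is (d²/4) × (2/9) = d²/18. Setting this to 0.17² gives d = 0.17 × √18 = 0.72 SD. As a check, the contrast of mean follow-up minus baseline has variance 0.75 at rho = 0.5, so SE = √0.75 × √(2/62) = 0.156. Then (0.72/0.156)² is again about 21.5.

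**3. Precision of the PosA main effect, 62 versus 62.** SE = √(2/62) = 0.180 SD, or 0.180 × √0.75 = 0.156 SD baseline-adjusted.

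- 95% CI half-width: 1.98 × SE = 0.36 SD, or 0.31 SD adjusted.
- Margin giving 80% power in two one-sided tests when the true effect is zero: (1.645 + 1.282) × SE = 0.53 SD, or 0.46 SD adjusted.

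| Size (SD) | Difference test non-significant if this is the true effect | Equivalence power if this is the margin and the true effect is 0 |
|---|---|---|
| 0.2 | 80% (75% adjusted) | 0% (0%) |
| 0.3 | 61% (51%) | 2% (22%) |
| 0.4 | 40% (27%) | 44% (65%) |
| 0.5 | 21% (11%) | 75% (88%) |

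At 0.72 SD the difference test misses in about 2% of trials or fewer, and equivalence power at that margin is 98% or more.

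**4. Precision of the simple effects, 31 versus 31.** SE = √(2/31) = 0.254 SD, or 0.220 SD adjusted. The 95% CI half-width is 0.50 SD, or 0.44 SD adjusted.

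**5. Do predictions 2 and 3 fit together?** Write T1 to T4 for mean TD in arms 1 to 4.

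- Pooled reading: (T1 + T2)/2 = (T3 + T4)/2, so T2 − T4 = −(T1 − T3). Prediction 3 requires T1 < T3, so T2 must exceed T4 by the same amount. If arm 1 is 0.3 SD below arm 3, PosA alone must be 0.3 SD above the control.
- Single-arm reading: T2 = T4 with T1 < T3 is an ordinary interaction and needs no rise under PosA alone. The pooled effect is then not zero but half of T1 − T3, so the pooled contrast would not test prediction 2.

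**The case against.** Three stronger conclusions are tempting, and the documents do not support them.

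- **That predictions 2 and 3 flatly contradict each other.** Prediction 2 speaks of the PosA condition in the singular. Study Design uses the word condition for a single arm, and Intervention Content calls arm 2 the PosA intervention. Read that way, the predictions are compatible, and the planned interaction and expected synergy fit. The plural neutral affect comparator and the factorial design favour pooling but do not settle it. The cited finding that PosA raises TD is background, not a prediction. It even supplies the direction that the pooled reading needs, although a purely additive rise would put arm 1 above arm 3, against prediction 3.
- **That the sample cannot exclude effects of the size planned for.** A reader might double 0.17 to get 0.34 SD. That conversion belongs to two groups measured once. For the four-arm, three-period interaction that reproduces the stated power, the corresponding PosA effect is about 0.72 SD, which this sample can exclude.
- **That the investigators will declare the null prediction confirmed.** The article nowhere says so.

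It can also be said that interval rules are commonly left to an analysis plan, that this is a condensed article, and that the study calls itself a pilot. So the absence of a margin is not in itself a fault. What stands is that the article states a no-difference prediction on a primary outcome and ties TD to tests and a sample size that address only differences.

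**Conclusion.** The point holds in two limited parts. First, the planned ANOVA tests cannot support prediction 2. With 124 analysed, the PosA main effect is known to within about 0.31 to 0.36 SD, and absence of an effect can be shown with 80% power only for margins of about 0.46 to 0.53 SD or wider. Effects near 0.72 SD can be excluded; an effect of 0.3 SD would go undetected in roughly half or more of trials.

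Second, prediction 2 is ambiguous between a main effect and a simple effect. Under the first it needs a rise in TD with PosA alone that is never predicted; under the second it is coherent but rests on 31 versus 31.

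These figures depend on 20% attrition, on SD-scaled TD and, for the adjusted values, on a correlation of 0.5. The 0.72 SD figure depends on reading 0.17 as the interaction f, with a correlation of 0.5 needed to reproduce 95% power. The sample size calculation itself is not at fault.

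**What to change.** - State whether prediction 2 is the PosA main effect or arm 2 against arm 4. Give the expected TD order of the four arms and reconcile it with the background statement that PosA raises TD.
- Report the PosA main effect (62 versus 62) and the PosA-by-EFT interaction on TD with 95% CIs. Give arm 2 against arm 4 and arm 1 against arm 3 as supporting estimates, noting their half-width of 0.44 to 0.50 SD.
- Claim no difference only if the 90% CI lies within a margin fixed before analysis. Otherwise report the result as inconclusive.

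The cost is wording and one interval rule, with no new data; recruitment was still open when the article was submitted. The drawback is that, unless a margin of about 0.5 SD or wider can be justified, the PosA effect on TD will often have to be called inconclusive. If prediction 2 is the simple effect, the margin that can be shown is wider still: 2.927 × 0.220 = 0.64 SD to 2.927 × 0.254 = 0.74 SD for 80% power.

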## Methods

### Study Design

This study is a factorial, randomized, controlled pilot study that employs a 2 (PosA imagery: positive, neutral) by 2 (EFT: yes, no) design in which participants are randomized to 1 of the 4 arms. Figure 1 shows the flow diagram depicting the experimental design. The 4 intervention arms are listed below:

Arm 1: PosA-EFTArm 2: PosA and *no* EFTArm 3: neutral affect and EFTArm 4: neutral affect and *no* EFT (ERT control condition)

### Sample Size

The target sample size of 156 participants (39 participants per group) is based on 2 prior studies testing EFT interventions. Sze et al [22] found that Web-based training in EFT (vs ERT) reduced TD with an effect size of *η*^2^=0.18. O’Neill et al [23] found that smartphone-delivered training in future (vs recent) episodic thinking impacted food choice by reducing total calorie consumption (*η*^2^=0.28) and percent calories consumed from fat (*η*^2^=0.28). We plan to use a mixed-design analysis of variance (ANOVA) with treatment arm (4 arms) as the between-subject variable and measurement period (baseline, after allocation, and closeout) as the within-subjects variable. As the EFT cue utilized by O’Neill et al was personalized to each participant and was delivered repeatedly via smartphone, and this protocol includes none of those design features (the intervention content is standardized and delivered once), we predict a smaller effect size. To be conservative, we predict the interaction between time and intervention arm variables will yield a standardized effect size of 0.17. Attrition rates commonly observed in brief guided imagery intervention studies are approximately 20% [32,33]. Therefore, we aim to recruit 156 total participants (39 participants per group) to allow for an analytic total sample of 124 participants with 31 participants in each group. This would provide 95% power to detect a statistically significant interaction between intervention arm and measurement period at the .05 level while adjusting for attrition.

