### Experimental Sessions

The study protocol includes 2 in-lab experimental sessions separated by approximately 5 days of at-home daily food diary entries (see Table 1). All questionnaires, intervention content, and baseline and outcome measures are delivered via the Qualtrics Web-based survey platform. Participants will be asked to fast for 2 hours before each experimental session, and all sessions will be scheduled after 10:00 am.

During the first experimental session, the participants will complete a battery of questionnaires, a baseline TD task, and a baseline food demand task (see the Primary Outcome Measures section below). Then, they will be randomly assigned to receive 1 of the 4 guided imagery intervention arms followed by manipulation check questions. Next, they will complete the TD and food demand tasks again, after which they will be offered a variety of snack foods to assess food choice. Food items will be placed next to the participants while a research assistant reads a standardized food choice script. At the end of the session, the participants’ anthropometric measurements will be taken, they will be scheduled for the second experimental session, and they will be instructed on when and how to complete the daily food diaries. The duration of the first session will be approximately 90 min, and each daily food diary entry will take approximately 5 min to complete. During the second experimental session, participants will complete the TD and food demand tasks again. They will be asked to complete another battery of questionnaires while they are again presented with a variety of snacks to eat, to assess their food choices a second time. The duration of the second session will be approximately 40 min. The schedule of enrollment, interventions, and assessments for the study is shown in Table 1.

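### For temporal discounting and food demand, the three-period repeated-measures ANOVA would drop participants who miss only visit 2, although their baseline and post-intervention data are already in hand

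*Protocol article*

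**What the plan says.** The Sample Size section of the protocol article plans a mixed-design ANOVA with "treatment arm (4 arms) as the between-subject variable" and "measurement period (baseline, after allocation, and closeout) as the within-subjects variable". It allows for attrition of about 20%: "Therefore, we aim to recruit 156 total participants (39 participants per group) to allow for an analytic total sample of 124 participants", which is 31 per arm. It then states: "This would provide 95% power to detect a statistically significant interaction between intervention arm and measurement period at the .05 level".

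Primary Statistical Analysis repeats the method for TD and the food demand indices: "A series of repeated measure ANOVAs with treatment arm as a between-subject variable and measurement period as the repeated measure will be conducted".

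Experimental Sessions gives the timing. Baseline TD and food demand come first at visit 1, then the guided imagery. Still at visit 1: "Next, they will complete the TD and food demand tasks again, after which they will be offered a variety of snack foods". Only the closeout measurement belongs to visit 2, about 5 days later. The one form of dropout given as an example, under Reimbursements, is failure to return for the second session.

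**The concern.** A classical repeated-measures ANOVA over three occasions deletes anyone with a missing occasion, and a planned analysis of 124 out of 156 fits that. Here the missing occasion would usually be closeout. A participant who does not come back has been randomised, has heard the recording, and has been measured before and after it. Nothing needed to estimate the immediate effect is missing, yet the person would not contribute to it.

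Two things are at stake. The immediate effect would be estimated with less information than was collected. It would also be estimated only in those who chose to return, a choice made after randomisation and after exposure to the intervention. If that choice depends on how people responded, and differently by arm, the comparison is no longer fully protected by randomisation.

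There is a related point about the three-period F test. Two measurements share one session of about 90 minutes and the third follows days later, so a higher correlation within the visit than across visits is plausible. An F test without a degrees-of-freedom correction would then be somewhat liberal.

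**Working it through.** **Inputs from the protocol article.** Four arms, three periods, alpha 0.05, power 95%, effect size 0.17, 124 analysed, 156 recruited, attrition about 20% (all Sample Size).

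**Assumptions, not in the document.** The effect size is read as Cohen's f for the arm-by-period interaction. The correlation between occasions is rho = 0.5. Sphericity holds (epsilon = 1) unless stated otherwise.

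**1. The plan's own figures.** For k arms, m periods and N participants, lambda = f² × N × m / (1 − rho), with (k−1)(m−1) and (N−k)(m−1) degrees of freedom.
- lambda = 0.17² × 124 × 3 / 0.5 = 21.50, with 6 and 240 degrees of freedom.
- Power = 0.951. The smallest multiple of 4 that reaches 95% is 124.
- Attrition: 124 / 0.8 = 155, or 156 as a multiple of 4.

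The stated power and both sample sizes reproduce. The result depends strongly on rho: power at 124 is 0.842 for rho = 0.3 and 0.998 for rho = 0.7.

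**2. How many people.** 156 − 124 = 32, and 32 / 156 = 20.5%. This is the number with usable visit-1 data only if every loss occurs after visit 1.

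**3. Cost for the immediate effect.** Information ratio 156 / 124 = 1.26; standard error ratio √(124 / 156) = 0.89. For the baseline-to-post comparison (m = 2, same f and rho):
- N = 124: lambda = 0.17² × 124 × 2 / 0.5 = 14.33, power 0.893.
- N = 156: lambda = 0.17² × 156 × 2 / 0.5 = 18.03, power 0.955.

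**4. Cost for the planned interaction test.** Generalised least squares information with an unstructured covariance, 31 complete plus 8 visit-1-only participants per arm, missing at random. The effect is scaled so that 124 complete cases give lambda 21.50.

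| Effect pattern | 124 complete | 124 complete + 32 visit 1 only | 156 complete |
|---|---|---|---|
| Post-intervention only, or sustained | 0.951 | 0.981 | 0.986 |
| Closeout only | 0.951 | 0.956 | 0.986 |

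The gain is in the immediate effect. Visit-1 data add little to an effect that appears only at closeout.

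**5. Sphericity.** No correlation is given, so the table shows a range. Type I error is for an uncorrected 4 × 3 interaction F with 31 per arm, simulated with 20,000 to 40,000 runs.

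| Within-visit / cross-visit correlation (assumed) | Type I error |
|---|---|
| 0.5 / 0.5 (sphericity) | 5.1% |
| 0.7 / 0.6 | 5.0% |
| 0.7 / 0.5 | 5.4% |
| 0.8 / 0.6 | 5.9% |
| 0.8 / 0.5 | 6.7% |
| 0.9 / 0.7 | 7.1% |
| 0.9 / 0.5 | 7.9% |

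With the other inputs unchanged, power at 124 is 0.909 when epsilon is 0.80 (0.8 / 0.5) and 0.859 when epsilon is 0.654 (0.9 / 0.5).

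**6. Which outcomes.** Steps 3 to 5 concern TD and food demand. Food choice has no baseline and two occasions, so sphericity is not at issue there, though a two-occasion repeated-measures ANOVA would likewise lose people with only the after-allocation value. Daily diary intake has a one-way ANOVA and is not affected by this point.

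**The case against.** The case on the other side has real weight.

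- **The sample was enlarged for attrition.** This stands. A reader might infer that the 95% power claim is wrong; it is not, because it is calculated at 124.
- **The protocol never says the F test is uncorrected.** This stands. A reader might infer that the schedule breaks sphericity and that the 5% test is therefore invalid. The document gives no correlations, and a correction can be left to an analysis plan that is not shown. The inflation is negligible for several plausible pairs of correlations.
- **The 32 are not shown to have visit-1 data.** This stands in part. The attrition rate is overall, and BMI is verified by measurements taken at the end of visit 1, after randomisation, so some losses could be ineligible participants. Thirty-two is an upper figure, and 156 for the immediate effect is a ceiling.
- **Bias from selective return is not demonstrated.** This stands. A reader might want to put a size on it, but that needs invented dropout slopes. Participants are not told the design, and payment for returning is the same in every arm. The bias is possible; its size is unknown.
- **Completers are not mentioned, and this is a pilot.** The word is indeed absent. But a three-period repeated-measures ANOVA with 124 of 156 analysed is a stated method with a stated sample, not a silence, and pilot status gives no reason to set aside data already collected.

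**Conclusion.** The point holds for TD and food demand as a matter of efficiency and of who is compared. Followed as written, the analysis would leave out up to about 32 participants whose baseline and after-allocation values exist, and would make the immediate effect conditional on returning after randomisation.

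With f = 0.17 and rho = 0.5, the loss is about 6 percentage points of power for the baseline-to-post comparison (0.893 against 0.955). For the planned interaction it is about 3 points if the effect is immediate or sustained, and about half a point if it appears only at closeout. Any selection bias cannot be sized from the document. Sphericity is a secondary reason to change the model: an uncorrected F would have a type I error between about 5% and 8%, depending on correlations that are not stated. It is worth changing, but it does not invalidate the design or the sample size.

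**What to change.** In Sample Size and Primary Statistical Analysis, replace the repeated-measures ANOVA for TD and food demand with a linear mixed model fitted by REML, with categorical period, unstructured covariance over the three occasions and small-sample degrees of freedom. Include all randomised participants with any measurement, analysed as allocated, and keep the planned demographic covariates. Report separate after-allocation and closeout contrasts. State that the after-allocation contrast uses everyone with visit-1 data (up to 156) and that closeout is expected to rest on about 124. For food choice, likewise keep participants who have only the after-allocation value.

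The unstructured covariance also removes the need for a sphericity assumption. The after-allocation contrast no longer depends on who returns. The closeout contrast still relies on data being missing at random given the visit-1 values.

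The cost is a change of analysis wording and slightly more analysis work. No extra data, visits or participants are needed. Recruitment was still under way at submission, with 84 participants having completed the protocol, so the change could be made before the final analysis.
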